### Subgroup analyses

We will evaluate treatment differences among subgroups defined by the following stratification variables: age group, sex, cancer comorbidity, AKI at study enrollment, abnormal kidney function using day 0 biomarker measurements (Table 2), total fluid volume received during intervention window, and country of enrollment. If there is significant heterogeneity in treatment effect using the Breslow-Day test [45], we will report separate results within strata.

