### Intervention

The intervention to be tested is predominant fluid resuscitation with balanced/buffered fluids (LR, Hartmann’s, or PlasmaLyte, as per local site preference) compared to the “usual practice” of predominant 0.9% saline resuscitation. Other than prescribing which crystalloid fluid type to use, the intervention will be implemented without efforts to standardize timing and volume of fluid resuscitation or other components of clinical care. Thus, all decisions to administer fluid, as well as timing, volume, and rate of fluid administration, remain at the discretion of the treating clinicians. Hospital fluid supplies will be used for this study without any change to packaging or labeling. Participants will be randomized to receive either balanced/buffered fluids or 0.9% saline for all bolus and maintenance fluid administration starting from randomization through 11:59 pm on the following calendar day. Maintenance fluids are included because these constitute a substantial proportion of total crystalloid fluid administration [35], including 40% of total crystalloids as maintenance fluids in our pilot study [25]. If the treating clinician deems it unsafe to continue study fluid or identifies a clinical indication that requires specific fluid or electrolyte therapy (e.g., hyponatremia, hyperkalemia, hypercalcemia, cerebral edema), non-study fluids are permitted. Use of non-isotonic fluids (e.g., 0.45% saline) is not recommended as standard maintenance fluids in children [36] and will be discouraged during the intervention phase. Colloid fluids and blood products may be administered at the discretion of the treating team.

Ending the intervention phase at 11:59 PM on the calendar day following randomization ensures all participants are eligible to receive study fluid for a minimum of 24 and a maximum of 48 h. This represents the time-window from the presentation during which most fluid resuscitation is completed for septic shock [17] and provides a pragmatic endpoint that signals the end of the intervention phase.

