Several potential threats to the validity of our trial exist. First, enrollment of children with suspected septic shock exclusively in the ED will include a wide range of illness severity and fluid exposure. Prior studies have demonstrated that fluid type has a negligible clinical impact when exposure is limited to low volumes [17, 18]. Therefore, we only include children who require > 1 fluid bolus *and* the fluid is directed to treat abnormal perfusion rather than dehydration or hypovolemia. This approach balances early enrollment, when it may not yet be clear how much fluid a patient may require, with enrichment of the study population by children for whom fluid type is most likely to have a clinical impact. In our pilot study using the same enrollment criteria, 42% were admitted to the intensive care unit [25], which represents the population with the highest exposure to study fluid and the greatest risk of achieving the primary outcome. A second threat is the lack of blinding. This decision was a practical one to constrain costs of providing blinded fluid bags across all parts of the hospital and needing additional safeguards if the treating physician was blinded to fluid type. However, we chose objective endpoints unlikely to be influenced by knowledge of study group assignment and will maintain blinding of the lead study statistician. Third, frequent withdrawal after EFIC or deferred consent could limit exposure to the intervention and/or impede outcome assessment. Although studies indicate < 1% withdrawal after EFIC or deferred consent [32, 52] and only 2% withdrew after EFIC in our pilot study [25], we plan to modify the analysis if missing data exceeds expectations. Finally, MAKE30 represents a composite of endpoints that may not be of equivalent value to patients or clinicians.

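### The fluid-volume subgroup is defined by a post-randomization variable, so its within-stratum comparisons are not protected by randomization

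*Protocol article*

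**What the plan says.** The Subgroup analyses section of the protocol article states: "We will evaluate treatment differences among subgroups defined by the following stratification variables". Seven variables follow, and "total fluid volume received during intervention window" stands in the list beside age group, sex, cancer comorbidity, AKI at enrollment and country. One rule serves all seven: "If there is significant heterogeneity in treatment effect using the Breslow-Day test [45], we will report separate results within strata". The Presentation of the results section adds that subgroup heterogeneity will be shown in forest plots.

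The Intervention section defines the window as "starting from randomization through 11:59 pm on the following calendar day" and leaves "timing, volume, and rate of fluid administration, remain at the discretion of the treating clinicians". The Blinding section says that clinicians know the allocation and that laboratory values reveal the crystalloid in use. The Discussion says that earlier studies showed that "fluid type has a negligible clinical impact when exposure is limited to low volumes". It also describes children admitted to intensive care as having both the highest exposure to study fluid and the greatest risk of the primary outcome.

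**The concern.** A subgroup comparison keeps the benefit of randomization only if the allocated treatment could not have changed who falls in which subgroup. Volume received in the window fails that condition in principle, because all of it is given after allocation, by clinicians who know the arm and see its biochemical effects. Early death or early renal replacement, both components of MAKE30, can also cut short the volume given.

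By the protocol's own account, volume also goes with prognosis. If one arm is given less fluid for the same severity, its children in any volume band are on average sicker than the other arm's children in that band. The within-band relative risk then mixes the effect of the fluid with a difference in severity.

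This matters for interpretation because the Discussion expects fluid type to have little effect at low volumes, which invites a dose-response reading of this subgroup. Elsewhere the article recognizes the hazard: for the per-protocol population, also defined by fluid received, the Statistical analysis section acknowledges confounding and plans covariate adjustment and an instrumental-variable analysis. The volume subgroup gets no such caveat. The Missing Data section reserves the hypothesis-generating label for analyses added later, so this one would carry the standing of a pre-specified analysis.

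**Working it through.** The plan states no figure for this subgroup, so there is none to reproduce. The check has two parts.

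**1. Is the variable post-randomization, and can it relate to both arm and outcome?**
- Timing: the window starts at randomization (Intervention), so none of the volume counted is a baseline quantity.
- Link to arm: possible, since volume is discretionary (Intervention) and allocation is known (Blinding). No section says that a difference is expected.
- Link to outcome: stated in the Discussion, as above.
- Table 4: its volume categories add pre-randomization fluid, while the subgroup counts only the window. Both contain post-randomization volume, so neither definition removes the problem.

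**2. How large could the distortion be?** The documents do not give the needed inputs, so these are assumptions:
- Severity U and noise e are independent standard normal.
- Log volume = log 60 + 0.6 × (0.6U + 0.8e), plus log(1 + s) in one arm. The median is 60 mL/kg and the correlation of severity with log volume is 0.6.
- MAKE30 risk = 1 / (1 + exp(3.35 − U)) in both arms. There is no treatment effect, overall risk is 5.1% and the overall relative risk is 1.00.
- Strata are <60, 60-100 and >100 mL/kg, borrowed from Table 4.

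Within each stratum, risk = E[risk(U) × P(stratum | U)] / E[P(stratum | U)]. The relative risk below is the lower-volume arm over the higher-volume arm.

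| Extra volume in one arm (s) | Relative risk in the three strata |
|---|---|
| 0% | 1.00 in all |
| 5% | 1.03-1.04 |
| 10% | 1.06-1.09 |
| 15% | 1.09-1.13 |

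For s = 10%, from low to high stratum, the unshifted arm has risks of 2.99%, 5.59% and 9.69%, and the shifted arm 2.80%, 5.15% and 9.13%. The ratios are 2.99/2.80 = 1.07, 5.59/5.15 = 1.09 and 9.69/9.13 = 1.06. If balanced fluid is the lower-volume arm it looks harmful in every stratum; if it is the higher-volume arm it looks beneficial in every stratum.

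**A second model as a check.** Volume = 70 + 25 × severity + noise (SD 20) mL/kg, control risk 6%, log-odds of 0.8 or 1.2 per SD of severity.
- True relative risk 1.00, balanced arm lower by 5 mL/kg: stratum values of about 1.07 (log-odds 0.8) or 1.10-1.13 (log-odds 1.2).
- True relative risk 1.00, balanced arm lower by 10 mL/kg: about 1.14-1.16 or 1.20-1.26.
- True relative risk 4.3/6.0 = 0.717, balanced arm lower by 10 mL/kg: about 0.82-0.84 or 0.85-0.90, so a third or more of the true reduction is hidden.
- In every case the overall intention-to-treat relative risk stays at its true value apart from simulation error, and a zero shift leaves the stratum values at the truth.

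**The case against.** The strongest reply is that bias needs allocation to change volume, and nothing in the article says that it does. That stands. A reader might infer that the stratum estimates are certainly biased, but the documents do not support this: with equal volume distributions in the model, every stratum is correct. The supportable statement is that randomization does not protect the comparison.

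The second reply concerns size. With 8800/2 = 4400 per arm and the first model's stratum shares of 50%, 30% and 20%, the standard error of the log relative risk, √[2(1 − p)/(np)], is about 0.17, 0.16 and 0.15. A distortion of 1.04 to 1.13 is log 1.04 = 0.04 to log 1.13 = 0.12, so less than one standard error. This too stands: in a single trial the distortion would be hard to tell from noise. It would be systematic all the same, and the forest plot could display it.

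A reader might also infer that the bias would set off the rule on separate reporting. The model does not bear this out. Because the shift is nearly equal across strata, it is not heterogeneity. In 1,500 simulated trials of 8800 per setting, Breslow-Day rejected in 4.0-6.1% with shifts of 5-15%, against 5.4% with none.

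Nor is the test's odds-ratio scale, set beside a relative-risk primary analysis, a material fault. A constant relative risk of 0.717 does give odds ratios of 0.71 and 0.66 at control risks of 3% and 25%. Yet even that wide assumed contrast raised rejection only to 6.8% at a nominal 5%, and Breslow-Day is a usual companion to Mantel-Haenszel.

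Finally, pre-randomization volume answers a narrower question than the one the Discussion raises. That is true and is a cost of the change.

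**Conclusion.** The point holds in this form: one of seven listed subgroups is defined by volume received after randomization, is treated like the baseline subgroups, and is liable to bias if the allocated fluid affects the volume given. Under the first model, a 5-15% volume difference distorts the relative risk by about 3-13%, in one direction across all strata. The second model gives up to about 26% at 10 mL/kg with the steeper severity gradient. These sizes rest on assumed correlations, volume distributions, cut-points and shifts; neither the size nor the direction in this trial can be known from the documents.

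The primary Mantel-Haenszel analysis, sample size, interim boundaries and secondary outcomes are unaffected. A reader might infer that the main result is threatened; it is not. The flaw is worth correcting because correction is cheap and this is the subgroup most open to a dose-response reading, but it is not a critical defect of the trial.

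**What to change.** Define the subgroup by a quantity fixed before randomization: crystalloid bolus volume given before randomization (already a row of Table 4), or total volume predicted from baseline variables only. Show received volume descriptively by arm, as Table 4 already intends.

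If received volume is kept as a subgroup, label it exploratory and non-randomized, set it apart from the baseline subgroups in the forest plot, and use a method suited to a post-randomization variable, such as principal stratification.

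The cost is a change to the subgroup list and its wording. No new data are needed, and the sample size does not change. The drawback is that pre-randomization volume is a weaker proxy for total exposure, since eligibility caps it at 40 mL/kg. A prediction from baseline variables needs a model specified before unblinding.

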### Missing Data

The primary ITT analysis will use complete case data if the percentage missing the primary outcome is ≤5% of total enrollment *and* all three country-specific percentages missing the primary outcome is ≤7% of country-specific enrollment. If these criteria are not met, we will use multiple imputation for the primary analysis with data assumed to be missing at random unless available data contradict this assumption. If the primary outcome is missing from between 1% and 5% of total participants, we will perform an adjunctive analysis using multiple imputation in addition to the complete case analysis. In addition, we will examine differences between participants with and without missing data and conduct a sensitivity analysis using the inverse-probability-weighting (IPW) method to conduct multiple imputation for the missing data [46, 47]. New analyses performed in addition to those described above will be delimitated as *post hoc* and considered hypothesis-generating.

### Presentation of the results

Trial results will be communicated to the public through manuscript publication and ClinicalTrials.gov, including the full study protocol and statistical code. Authorship will adhere to the *International Committee of Medical Journal Editors* guidelines. To ensure widespread access to study findings, we will seek publication using “open access”. After the publication of main and secondary results, a public use dataset will be submitted to the *Eunice Kennedy Shriver* National Institute of Child Health and Development Data and Specimen Hub (DASH).

The flow of participants through the study will be presented as in Fig. 3. Baseline characteristics will be presented by the treatment group, as in Table 3. Total, bolus, and maintenance volumes of crystalloid and other fluids and blood products will also be presented by the treatment group, as in Table 4. Laboratory data will be presented in figures displaying initial and follow-up values. All outcomes will be reported by the treatment group with both unadjusted frequencies and proportions, as well as with any statistical adjustments. Heterogeneity of treatment effect for subgroup analyses will be displayed within forest plots.

**Fig. 3 Fig3:**
[figure not shown]
Flow diagram of patients progressing through the trial

**Table 3 Tab3:** Patient characteristics

Characteristic	0.9% saline	Balanced/buffered fluid
	(*n* = )	(*n* = )
Country of enrollment, *n* (%)		
USA		
Canada		
Australia/New Zealand		
Age in years, median (IQR)		
Age category, *n* (%)		
6 mos to < 1 year		
1 year to < 5 years		
5 years to < 12 years		
12 years to < 18 years		
Sex, *n* (%)		
Male		
Female		
Other/unknown		
Race, *n* (%)		
White		
Black		
Asian		
American Indian/Alaska Native		
Native Hawaiian/Other Pacific Islander		
Unknown/not reported^a^		
Ethnicity, *n* (%)		
Hispanic or Latino		
Aboriginal or Torres Strait Islander		
Maori		
Other^b^		
Unknown/not reported^a^		
Weight (kg), median (IQR)		
Comorbid conditions, *n* (%)		
Cancer (hematogenous or solid tumor)		
Bone marrow or solid organ transplant		
Cardiomyopathy or heart failure		
Pulmonary hypertension		
Kidney disease (not on dialysis)		
Neurologic dysfunction causing severe developmental delay		
Sickle cell disease		
Chronic ventilator dependence		
Indwelling central line		
Site of infection, *n* (%)		
Primary bloodstream		
Pneumonia or other lung infections		
Abdominal		
Genitourinary		
Central nervous system		
Skin/soft tissue		
Other infection		
Unknown site		
Alternative diagnosis (not infection)		
Positive blood culture (bacteremia) as either primary or additional site of infection, *n* (%)		
Concurrent Therapies (through study day 1, 11:59 pm)		
Antibiotics prior to study site ED arrival, *n* (%)		
Minutes to first antibiotic administration after ED arrival, median (IQR)^c^		
Ceftriaxone, *n* (%)		
Vasoactives, *n* (%)		
Corticosteroids, *n* (%)		
Bicarbonate or other buffers, *n* (%)		
Invasive mechanical ventilation^d^, *n* (%)		
Extracorporeal membrane oxygenation, n (%)		
Baseline creatinine (mg/dL)^e^, median (IQR)		
KDIGO acute kidney injury stage at enrollment, *n* (%)		
Stage 1		
Stage 2		
Stage 3		

*KDIGO*, Kidney Disease: Improving Global Outcomes

^a^Race and ethnicity not available from participants enrolled in Canadian sites

^b^“Other” ethnicity includes participants who identified as not Hispanic or Latino in the USA and not Aboriginal or Torres Strait Islander or Maori in Australia/New Zealand

^c^Includes only the subset of participants (*n* = ) who did not receive antibiotics prior to study site ED arrival

^d^Includes only invasive mechanical ventilation delivered through an endotracheal tube (oral or nasal), tracheostomy, laryngeal mask airway, or other invasive devices

^e^Baseline serum creatinine is the lowest creatinine available between 12 months and 24 h prior to study enrollment or, for participants without such data, an imputed value using established median values for age and sex

**Table 4 Tab4:** Fluid administration

Characteristic	0.9% saline	Balanced/buffered fluid	Difference (95% CI)
	(*n* = )	(*n* = )	
Number of crystalloid fluid boluses, median (IQR)			
Total^a^			
Prior to randomization			
During intervention phase			
Crystalloid volume administered (mL/kg), median (IQR)			
Total fluid (bolus and maintenance)^a^			
Any crystalloid			
0.9% saline			
Balanced/buffered fluid			
Bolus fluid only			
Prior to randomization			
During intervention phase			
0.9% saline			
Balanced/buffered fluid			
Maintenance fluid only			
Any crystalloid			
0.9% saline			
Balanced/buffered fluid			
Other			
Colloid volume administered (mL/kg), median (IQR)			
Albumin 4%/5%			
Other			
Blood product volume administered (mL/kg), median (IQR)			
Red blood cells			
Platelets			
Plasma or cryoprecipitate			
Other			
Fluid volume categories^a^, *n* (%)			
Total crystalloid (bolus and maintenance)			
<60 mL/kg			
60–100 mL/kg			
>100 mL/kg			
Bolus fluid only			
<60 mL/kg			
60–100 mL/kg			
>100 mL/kg			
Protocol Adherence			
Received ≥75% of total crystalloid as randomized fluid type during intervention phase, *n* (%)			

^a^Includes fluid administered prior to randomization and during the intervention phase

## Discussion

PRoMPT BOLUS will provide high-quality evidence for the comparative effectiveness of buffered/balanced crystalloids versus 0.9% saline for the initial fluid management of children with suspected septic shock in emergency settings. Currently, there is insufficient evidence to support one crystalloid fluid type for pediatric shock resuscitation, which was acknowledged as a key knowledge gap by the 2020 Surviving Sepsis Campaign guidelines [21, 22]. Should balanced/buffered fluids improve outcomes compared to 0.9% saline, this practice change could be quickly implemented given that these fluids are readily accessible. Thus, the results of this trial could be rapidly incorporated into clinical practice with an immediate impact on the health of children worldwide. Conversely, because this trial is powered to detect small clinical differences, a finding of no difference between groups would signify that the initial choice of crystalloid fluid type is inconsequential for most children with septic shock during the initial 24-48 hour resuscitation period.

We selected a pragmatic design for several reasons [48, 49]. First, embedding enrollment into routine care will reduce cross-over by minimizing pre-enrollment exposure to non-study fluids. Second, a pragmatic protocol allows flexibility to execute the study across multiple sites, countries, and healthcare systems. Third, loosening reliance on a study team allows study procedures to continue across multiple hospital units and providers. Finally, generalizability is optimized by using a study protocol that mirrors the variance in clinical decision-making outside of this study.

The decision to use patient-level randomization rather than an alternative method based on systematic allocation (e.g., different fluid type in alternating months) or cluster randomization ensured that allocation concealment was maintained until after patient enrollment despite not blinding the study intervention. We were concerned that pre-enrollment awareness of treatment allocation could lead to selection bias. Importantly, there was no allocation strategy we believed could eliminate cross-over between groups. Selection of fluid type is dictated by multiple factors, including a potential lack of personal equipoise across providers, numerous clinical indications for specified fluid and electrolyte titration, ongoing debate about the utility of acid buffers in acutely ill patients [50, 51], and imperfect awareness of study enrollment. However, a tolerance of some use of non-study fluid after enrollment will mimic real-world conditions where cross-over between fluid types is common. As such, we defined adherence as receipt of ≥75% of total crystalloid administered by type randomized. Therefore, our study is most appropriately construed as the comparative effectiveness between the *predominant*—rather than exclusive—use of balanced/buffered fluids versus 0.9% saline. Even if exclusive use of a single fluid type could be executed under controlled experimental conditions, it is unlikely that such a practice could be generalized to real-world fluid management.

Several potential threats to the validity of our trial exist. First, enrollment of children with suspected septic shock exclusively in the ED will include a wide range of illness severity and fluid exposure. Prior studies have demonstrated that fluid type has a negligible clinical impact when exposure is limited to low volumes [17, 18]. Therefore, we only include children who require > 1 fluid bolus *and* the fluid is directed to treat abnormal perfusion rather than dehydration or hypovolemia. This approach balances early enrollment, when it may not yet be clear how much fluid a patient may require, with enrichment of the study population by children for whom fluid type is most likely to have a clinical impact. In our pilot study using the same enrollment criteria, 42% were admitted to the intensive care unit [25], which represents the population with the highest exposure to study fluid and the greatest risk of achieving the primary outcome. A second threat is the lack of blinding. This decision was a practical one to constrain costs of providing blinded fluid bags across all parts of the hospital and needing additional safeguards if the treating physician was blinded to fluid type. However, we chose objective endpoints unlikely to be influenced by knowledge of study group assignment and will maintain blinding of the lead study statistician. Third, frequent withdrawal after EFIC or deferred consent could limit exposure to the intervention and/or impede outcome assessment. Although studies indicate < 1% withdrawal after EFIC or deferred consent [32, 52] and only 2% withdrew after EFIC in our pilot study [25], we plan to modify the analysis if missing data exceeds expectations. Finally, MAKE30 represents a composite of endpoints that may not be of equivalent value to patients or clinicians.

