The primary aim of the Pragmatic Pediatric Trial of Balanced versus Normal Saline Fluid in Sepsis (PRoMPT BOLUS) is to determine if resuscitation with balanced/buffered fluids as part of usual care will improve outcomes compared to 0.9% saline for children with septic shock. Secondary aims are to compare the relative safety and determine the differential effect of each fluid type on kidney injury biomarkers in children with septic shock. We hypothesize that balanced/buffered fluid resuscitation will reduce MAKE30 (a composite of death, new RRT, or persistent kidney dysfunction) compared to 0.9% saline, in part through reduced kidney injury, without an increase in adverse effects. Notably, even a small clinical benefit would be important because sepsis is common, life-threatening, and the proposed practice change is inexpensive and readily available.

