### Participants

All patients > 6 months to < 18 years treated for suspected septic shock with parenteral antibiotics and at least one fluid bolus for abnormal perfusion in a study site ED will be eligible for study enrollment. The lower age was selected to adhere to the US Food and Drug Administration (FDA) warning that infants < 6 months may have reduced hepatic capacity to metabolize exogenous lactate in LR. “Suspected septic shock” is operationalized as a) the treating clinician’s diagnosis of septic shock and/or treatment that includes parenteral antibiotic and fluid resuscitation for abnormal perfusion or b) a sepsis alert on a site-specific screening tool with clinician confirmation to proceed with treatment for suspected septic shock. Abnormal perfusion is defined as the treating clinician’s judgment that hypotension or abnormal (either “flash” or “prolonged”) capillary refill is present. To reflect usual clinical practice, we do not define thresholds for hypotension or abnormal capillary refill but rather defer to the treating clinician’s discretion to differentiate abnormal from normal. Recognizing that fluid resuscitation may start prior to ED arrival, only those for whom total volume of crystalloid fluid administration can be confirmed as ≤40 mL/kg will be eligible.

Exclusion criteria are (1) clinician judgment that the patient’s condition deems it unsafe to administer either 0.9% saline or balanced/buffered fluids (see Additional file 2), (2) known pregnancy at time of assessment for eligibility, (3) known prisoner at time of assessment for eligibility (in USA, Australia/New Zealand), (4) patient is a ward of the state (in Australia/New Zealand), (5) known allergy to either fluid type, or (6) prior indication that patient would not agree to be enrolled in the study.

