### Sample size

A baseline incidence of MAKE30 in children with septic shock predominantly resuscitated with 0.9% saline was determined based on a prior pediatric study (9.6% MAKE30) [39], the proportion of patients aged 18–21 years enrolled in the SMART trial (9.7% MAKE30) [17], and institutional registry data from two US study sites (5.0% and 7.8% MAKE30). We anticipate a conservative MAKE30 incidence of 6% among children treated in an ED for suspected septic shock largely resuscitated with 0.9% saline. Enrollment of 8800 total participants will provide 95% power to detect an absolute risk reduction (ARR) in MAKE30 from 6.0% for children treated with 0.9% saline to 4.3% for balanced/buffered fluids with a standard type I error of 0.05. This ARR corresponds to the 28% relative risk reduction in MAKE30 observed in the youngest subset of patients (18–21 years) enrolled in SMART. Due to the small anticipated ARR with potential for type II error, we purposely selected a high power of 95% for the primary endpoint. This sample size will also provide 84% power to detect a decrease in mortality from 3% with saline to 2% with balanced/buffered fluids and > 99% power to detect a 1-day reduction in hospital-free days.

Recruitment of this large sample size requires collaboration across > 40 sites from three research networks. Based on the enrollment of 85% of eligible patients in our pilot study [25], sites are anticipated to enroll > 80% of eligible patients. Recruitment will be monitored, with targeted support provided to sites that consistently fall below this target. Targeted support will include local investigators meeting with the lead investigators from their respective networks to review the process for screening, determination of eligibility criteria, education of local emergency clinicians who assess for eligibility, location of enrollment materials relative to patient care in the emergency department, and tracking of reasons for missed enrollments. If enrollment fails to demonstrate improvement toward or above the > 80% target despite these efforts, the site will be considered for removal from study participation and a replacement site will be identified.

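### The Discussion would read a null result as showing that fluid type is inconsequential, but the 95% power behind that reading applies only to a 1.7-point (28% relative) reduction in MAKE30

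*Protocol article*

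**What the plan says.** The Discussion states that "a finding of no difference between groups would signify that the initial choice of crystalloid fluid type is inconsequential" for most children, in the first 24 to 48 hours. Its reason is that "because this trial is powered to detect small clinical differences".

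The Sample size section gives 95% power with 8800 participants for a fall in MAKE30 from 6.0% to 4.3% at a type I error of 0.05. It adds: "This ARR corresponds to the 28% relative risk reduction in MAKE30 observed in the youngest subset of patients" of an adult trial, and describes the anticipated absolute reduction as small. The Statistical analysis section sets the final significance level at 0.044. The Background frames a superiority hypothesis and says that "even a small clinical benefit would be important because sepsis is common, life-threatening, and the proposed practice change is inexpensive and readily available". It gives no threshold for small.

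On a related matter, the Discussion says "we only include children who require > 1 fluid bolus", as a safeguard against enrolling children with little fluid exposure. The Participants section says that patients with "at least one fluid bolus for abnormal perfusion in a study site ED will be eligible".

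**The concern.** A superiority test that fails to reject does not show absence of effect. What a null result supports depends on the confidence interval and on the smallest effect that would matter. The Discussion instead infers from the planned power that no difference means fluid choice does not matter. High power for one effect size supports that inference only against effects of that size or larger. The Background values even a small benefit, because the condition is common and the change is cheap.

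At stake is the conclusion drawn from a null trial. The Discussion expects the results to be taken quickly into practice. If the sentence guides the final report, a result still compatible with a moderate benefit could be presented as settling the question.

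**Working it through.** **Inputs.** 8800 participants in equal allocation, so n = 4400 per arm (Sample size; Randomization and allocation concealment). Rates 6.0% and 4.3%, type I error 0.05 (Sample size). Final level 0.044 (Statistical analysis). Two-sided testing, as for the monitoring boundaries (Data/safety monitoring and interim analysis). Critical values: z = 1.960 for 0.05 and 2.014 for 0.044.

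**Step 1: reproduce the plan's figure.** Power = Φ[(d − z·SE0)/SE1], where d is the risk difference, SE0 = √(2p̄(1−p̄)/n) and SE1 = √((p1(1−p1) + p2(1−p2))/n).

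- p̄ = 0.0515, so SE0 = √(2 × 0.0515 × 0.9485/4400) = 0.004712.
- SE1 = √((0.0564 + 0.041151)/4400) = 0.004709.
- At 0.05: (0.017 − 1.960 × 0.004712)/0.004709 = 1.649, power 95.0%.
- At 0.044: (0.017 − 2.014 × 0.004712)/0.004709 = 1.595, power 94.5%.

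The stated 95% is correct.

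**Step 2: power for smaller effects**, with 6% in the saline arm and the same formula.

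| Relative reduction | Points | Power at 0.044 | Power at 0.05 |
|---|---|---|---|
| 25% | 1.5 | 87% | 88% |
| 20% | 1.2 | 68% | 70% |
| 17% | 1.0 | 52% | 54% |
| 15% | 0.9 | 43% | 45% |
| 10% | 0.6 | 21% | 23% |

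The effect detectable with 80% power is about 1.4 points (about 23% relative).

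**Step 3: interval if both arms observe 6%.**

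- Risk difference: SE = √(2 × 0.06 × 0.94/4400) = 0.506 points; 2.014 × 0.506 = 1.02 points. With 1.960 it is 0.99.
- Relative risk: SE of the log = √(2 × 0.94/(4400 × 0.06)) = 0.0844; exp(±2.014 × 0.0844) = 0.84 to 1.19.

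So 1.7 points is excluded, and benefits up to about 1.0 point are not.

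**Step 4: a just non-significant result.** Take 6.0% versus 5.03%. The test statistic is 1.993, below 2.014. The interval for the reduction runs from about −0.01 to 1.95 points (relative risk about 0.70 to 1.00), so it contains the 1.7-point design effect.

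To see where exclusion of 1.7 points stops, take an observed reduction of 0.70 points (6.0% versus 5.3%). The half-width is 2.014 × √((0.0564 + 0.050191)/4400) = 0.99 points, so the upper limit is 0.70 + 0.99 = 1.69. Non-significant results with observed reductions from just above 0.7 to 0.97 points therefore leave the design effect open.

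**Step 5: bolus count, illustration only.** Assume that 20% of enrolled children have a single bolus and no treatment effect, the overall saline rate stays at 6%, and the others have relative risk 4.3/6.0.

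- Equal baseline risk in both groups: the overall reduction is 0.8 × 1.7 = 1.36 points and power at 0.044 is about 80%.
- Single-bolus children at a quarter of the others' risk: the others' rate is 0.06/0.85 = 7.06%, the overall reduction is 0.8 × 7.06 × 0.283 = 1.60 points and power is about 91%.

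The 20% share and the zero effect do not come from the document.

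**Limits.** These are normal approximations to a single unstratified comparison with complete outcomes. The site-stratified Mantel-Haenszel analysis and the interim looks were not modelled.

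**The case against.** The strongest reply is that the Discussion uses small as the Sample size section does, for the 1.7-point reduction. Against that target the inference works: an observed difference near zero would exclude 1.7 points. The sentence is also limited to most children and to the first 24 to 48 hours, and it speaks of a finding of no difference, not of any non-significant test. All of this stands. It does not cover a non-significant result with an observed reduction between about 0.7 and 0.97 points, nor does it make benefits below 1.7 points inconsequential.

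Several stronger readings are tempting, and the document does not support them.

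- A reader might infer that the trial cannot exclude benefits that the plan itself calls important. No passage names a MAKE30 benefit below 1.7 points as important. The Sample size section does power for a 1-point fall in mortality (3% to 2%), which suggests interest in effects of that size, but that is a different outcome.
- A reader might take the sentence as a binding analysis rule. It is an interpretive remark in the Discussion and changes no analysis. The full protocol and the analysis plan are not shown, so a criterion based on the interval cannot be called missing.
- A reader might say flatly that a benefit of 1 child in 100 is not excluded. At equal rates of 6% that turns on the multiplier (1.02 versus 0.99 points), so only about 1.0 point is defensible.
- A reader might think that the claim rests on the entry rule of more than one bolus. The sentence gives power as its only reason. The bolus contradiction is real but separate. A subgroup analysis by total fluid volume is also planned, so effects by exposure would be visible.

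**Conclusion.** The point holds as a fault in stated interpretation, not in sample size or analysis. The 95% power is right for 1.7 points. It does not justify calling fluid type inconsequential after a null result, because power is about 68% for a 20% relative reduction and 43% for 15%, and even identical observed rates leave a benefit of about 1.0 point inside the interval. These figures assume 4400 evaluable children per arm and a 6% saline rate.

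The one-bolus and more-than-one-bolus statements contradict each other on the face of the text. How far this would dilute the effect cannot be known from the document; the 80% to 91% range is illustrative.

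**What to change.** Replace the sentence with a statement to this effect: a non-significant result will be interpreted from the confidence interval for the MAKE30 difference, naming the effects it does and does not exclude, in particular whether it excludes the 1.7-point design effect; non-significance will not by itself be called evidence that fluid type is inconsequential.

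If the sponsor wishes to keep that word, it should fix the smallest difference it regards as important before unblinding. That choice has consequences. With a margin of ±1.7 points and no true difference, the interval would fall inside with probability of about 2Φ((1.70 − 1.02)/0.506) − 1 = 82%, but a 1-point benefit could still lie within it. A margin of 1.0 point could not be met even by equal observed rates of 6%, where the half-width is 1.02.

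Separately, reconcile the bolus count in the Participants section with that in the Discussion, so that eligibility and the enrichment claim agree.

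The cost is wording, plus a decision on the margin if the stronger word is kept. The downside is a more cautious conclusion from a null result.
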